#### Measures

***Physical activity***: Objective measures of PA will be obtained using Actigraph wGT3X-BT accelerometers (Actigraph LLC, Pensacola, FL). Decision rules will follow recommendations of Migueles, Cadenas-Sanchez [40] for use with Actigraph accelerometers. Data will be collected in 60 s epochs with a sampling frequency of 60 Hz and the normal filter. Non-wear-time will follow the Choi, Liu [41] algorithm. Days of PA measurement will be considered “valid” if the device is worn for 10 or more hours per day. Four or more days of wear is considered a “valid” measurement week. The main outcomes of interest are average steps per day, minutes of total PA per day, and minutes of moderate-to-vigorous PA (MVPA) per day.

Participants’ location will be tracked using Qstarz BT-Q1000XT Travel Recorder XT GPS devices. These are satellite-based global navigation systems that measure participants’ location every five seconds. A “valid” measurement week will be considered four or more days of wear. Exact GPS variables are still being finalized but will likely include transport and leisure walking. We plan to use the HABITUS software [42] to merge and process accelerometer and GPS data.

To supplement GPS and accelerometer measurements, participants will also complete a travel diary and logbook. They will record their wake and bedtimes, and times when the devices are taken off, and details on where they travel.

Self-report measures of leisure and transport PA from the past seven days within the neighbourhood will be measured using the Neighbourhood – International Physical Activity Questionnaire (N-IPAQ)[43]. Self-reported stair climbing will be assessed with the question “How many total floors of stairs throughout the day do you walk UP on an average weekday at your CURRENT home building?” (responses: 0 floors, 1–2 floors, 3–6 floors, 6 or more floors, unable to walk up the stairs).

***Dietary assessment***: Frequency of fruits and vegetable, salty food, and sugar-sweetened beverage consumption will be assessed using a food frequency questionnaire adapted from the Nutritional Environment Measures Survey – Perceived Nutrition Environment (NEMS-P)[44].

***Social connections***: Connections to people in one’s neighbourhood will be captured using survey questions of sense of belonging [45], community satisfaction [46], local social ties [47], and social cohesion and trust [48].

***Capability, Opportunity, and Motivation***: Physical opportunity will be assessed as perceptions of healthy food access in the neighbourhood using the NEMS-P [44]. Items will assess access to stores and restaurants, store availability of healthy food choices, store prices of fruits and vegetables, store placement of healthy items and nutrition information, availability of healthy options at restaurants, restaurant promotion of healthy options and nutrition information, and costs of healthy options at restaurants.

Physical opportunity will be assessed as perceptions of neighbourhood supports for PA using the Physical Activity Neighbourhood Environment Scale (PANES)[49]. This scale captures residential density, land mix use, street connectivity, proximity to neighbourhood recreation facilities, pedestrian infrastructure, bicycling infrastructure, aesthetic qualities, social cues for PA, traffic and crime safety, and access to a working automobile.

Physical capability around PA will be assessed using two questions from the short form health survey (SF-12)[50]. Two questions on functional limitations ask “Does your health now limit you in these activities? If so, how much?” Activities include (a) moderate activities such as moving a table, pushing a vacuum cleaner, bowling, or playing golf, and (b) climbing several flights of stairs.

Questions on motivation, capability, and social opportunity may be assessed using generic items designed specifically for the COM-B [51]. Specific outcomes included in these questions will be selected based on the final design and amenity intervention elements that are implemented at the site(s). For example, if healthy stairwell design elements are implemented, then stair climbing will likely be included as an outcome.

***Body mass index (BMI)***: Measurements of height and weight will be taken using the Canadian Physical Activity, Fitness and Lifestyle Appraisal procedures [52]. Specifically, body weight in Kilograms (nearest 0.1 kg) and height in meters (nearest 1.0 mm) will be measured twice in each participant with light clothing and no shoes using a portable physician-grade stadiometer and scale (Health o Meter). BMI will be calculated as kg/m^2^.

***Socio-demographic information***: Age, gender, ethnicity, physical and mental health status, marital status, smoking and alcohol use, employment status, income, education, and falls in the past year, will be measured using standard questionnaire items.

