#### Procedures

Measurements will occur before and after changes to the BE and amenities are introduced. Residents moving into the new development(s), and current residents at the control site(s) will participate in one baseline measurement (3-6-months before move-in) along with two follow-up measurements if possible (3-6-months and 9-12-months post-move-in).

The researchers will visit the participants at the development where they live for a one to two hour scheduled appointment. First, researchers will describe the study and obtain written informed consent from residents regarding their willingness to participate. Second, participants will complete a survey on their health and health behaviours, perceptions of their neighbourhood environment, and socio-demographic characteristics. Third, their height and weight will be measured using a standiometer and scale. Fourth, they will be asked to wear an accelerometer and Global Positioning System (GPS) device on a waistband for seven consecutive days during all waking hours and to complete a logbook and travel diary. They will be trained on how to position the accelerometer on their right hip and the GPS on their left hip. Participants will receive a $20 gift card for participating in all parts of the study.

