#### Analyses

Differences in baseline characteristics (e.g., demographic factors and outcome measures) of residents in the intervention and control site(s) will be investigated using independent samples t-tests. Any differences identified may be considered as covariates in the main analyses. We will attempt to control for any unusual events and socio-economic or political influences that occurred during the study period. Covariates may include age, gender, building site, functional ability, car ownership, socio-economic status or other demographic variables that differ between residents of intervention and control sites at baseline.

We intend to run a difference-in-difference analysis to test for differences between intervention and control groups in change from baseline to 3-6-month post-move-in, and change from baseline to 9-12-month post-move-in. The type of analysis will depend on the measurement unit of each outcome (e.g., linear regression for continuous outcome variables, logistic regression for categorical outcome variables). For the primary outcome of PA, a difference-in-difference linear regression analysis with a continuous outcome will have 80 % power with 107 participants for a model with five main predictor variables and three covariates at α = 0.05 [53].

Depending on how many units the final intervention and control sites have, data may be collected on couples and a multi-level modeling approach used to control for clustering within unit. The approach that is best able to maximize power will be chosen.

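### Alpha of 0.05 and 80% power are stated for one primary outcome, PA, but the article names three main PA outcomes at up to two follow-ups and designates none as primary

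*Protocol article*

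**What the plan says.** Under Quantitative resident evaluation, Analyses, the protocol article introduces its sample size with "For the primary outcome of PA, a difference-in-difference linear regression analysis with a continuous outcome", which "will have 80 % power with 107 participants" "for a model with five main predictor variables and three covariates at α = 0.05". This is the only alpha in the article, and the outcome is in the singular.

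Under Measures, Physical activity, the accelerometer outcomes are given as a list of three with no ranking: "The main outcomes of interest are average steps per day, minutes of total PA per day", followed by daily MVPA minutes as the third.

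The Analyses section also sets the contrasts. Intervention and control groups are to be compared on "change from baseline to 3-6-month post-move-in, and change from baseline to 9-12-month post-move-in". Neither contrast is called primary. The Procedures section makes the number of visits conditional: one baseline "along with two follow-up measurements if possible (3-6-months and 9-12-months post-move-in").

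**The concern.** A sample size and an alpha describe one test of one variable at one time. Here they are attached to a label, PA, that the same article unpacks into three variables and up to two change scores. A reader cannot tell which of the contrasts has 80% power, or which must be significant for the study to conclude that PA improved.

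Two things are at stake. If the choice is left until results are known, whichever contrast is significant could be presented as the primary result, and the chance of a false primary claim would exceed the 5% in the power sentence. If instead all contrasts are kept as primary and the error is controlled, 107 participants no longer give 80% power for each.

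**Working it through.** **Inputs from the article.** Three main accelerometer outcomes (Measures). Two change contrasts (Analyses), the second follow-up conditional (Procedures). Alpha 0.05, N = 107, power 80%, five main predictors plus three covariates, so 8 in all (Analyses). The number of contrasts is 3 × 1 = 3 or 3 × 2 = 6.

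**Inputs assumed.** The article gives no effect size and no correlations. Cohen's f² = 0.15 is assumed for the sample-size check, and ranges of correlation are assumed for the error rates.

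**Step 1: the plan's own figure.** Power of an F-test with u numerator degrees of freedom and p = 8 predictors comes from the noncentral F distribution with denominator degrees of freedom v = N − p − 1 and noncentrality λ = f²N.

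- Overall test (u = 8), f² = 0.15, N = 107: v = 98, λ = 16.05, power 79.4%. The N for 80% is 109, close to the stated 107.
- Five main predictors jointly (u = 5), same f²: N = 92.
- One coefficient (u = 1), same f²: N = 55. At N = 107, a one-coefficient test reaches 80% power at f² = 0.075.

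The figure is thus roughly recovered for one regression of one continuous outcome at an undivided alpha of 0.05. Nothing in it identifies the variable or the visit.

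**Step 2: error rate if every contrast is tested at 0.05 and any one counts.** For k independent tests the rate is 1 − 0.95^k.

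- k = 3: 1 − 0.857 = 14.3%
- k = 6: 1 − 0.735 = 26.5%

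The contrasts are not independent, so the rate was simulated: 2 million draws of correlated two-sided z-tests under no effect, with outcome correlation r_o and, for six tests, correlation r_t between the two visits' contrasts.

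| r_o | 3 tests (one visit) | 6 tests, r_t = 0.5 | 6 tests, r_t = 0.7 | 6 tests, r_t = 0.9 |
|---|---|---|---|---|
| 0.3 | 13.6% | 23.8% | 22.0% | 18.8% |
| 0.5 | 12.5% | 21.9% | 20.2% | 17.2% |
| 0.8 | 9.8% | 17.3% | 15.9% | 13.5% |
| 0.9 | 8.4% | 14.9% | 13.7% | 11.5% |

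With the independent case as the upper end, three tests span 8.4 to 14.3% and six tests 11.5 to 26.5%.

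**Step 3: what 107 supports if all contrasts stay primary.** A Bonferroni split gives 0.05/3 = 0.0167 or 0.05/6 = 0.0083 per test.

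| Contrasts | Test (assumed f²) | Power at N = 107 | N for 80% |
|---|---|---|---|
| 3 | 8 df (0.15) | 64% | 136 |
| 3 | 1 df (0.075) | 65% | 143 |
| 6 | 8 df (0.15) | 55% | 153 |
| 6 | 1 df (0.075) | 56% | 166 |

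Bonferroni ignores the correlation between tests, so these figures are conservative.

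**The case against.** The strongest reply is that a journal article condenses the plan. Testing order, alpha allocation and the reading of a mixed result are commonly left to the full protocol or the SAP, and neither is shown. That stands: their absence is not the point here. What remains is internal to the article, which declares one primary outcome, attaches an alpha and a sample size to it, and elsewhere describes the same outcome as three main variables with two change contrasts.

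A reader might go further and infer that six primary tests are each made at 0.05, so that the chance of a false primary claim is about a quarter. The article does not support this. Alpha appears once, in the power sentence; no per-test threshold is given, and nothing says that one significant result suffices. The second follow-up is conditional. The section on setting reports delays already incurred against a grant ending in October 2023, so three contrasts is a realistic outcome. The three measures also overlap: MVPA minutes are part of total PA minutes, and steps come from the same device in the same week. High correlations are therefore plausible, and they point to the lower end of each range.

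A reader might also count the GPS, questionnaire and stair-climbing measures as further primary tests, especially as the article says "Exact GPS variables are still being finalized but will likely include transport and leisure walking". The article confines the main outcomes to the three accelerometer variables. The Discussion presents domain-specific PA as a way to learn which types of activity change. Nothing makes those measures primary.

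**Conclusion.** The point holds as a mismatch within the article: one powered primary outcome corresponds to three to six undesignated contrasts, so the stated alpha and power belong to no single test. That much needs no assumption.

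The size is conditional. It requires that each contrast be tested at 0.05 and that any significant result be read as PA having improved. Under that reading the false-positive rate is about 8 to 14% with three tests and about 11 to 27% with six, depending on correlations that the article does not give. Every case computed exceeds 5%; with highly correlated measures the excess is roughly twofold. The defect is worth correcting, is cheap to correct, and does not undermine the design.

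**What to change.** Before data collection, name one PA variable at one time point as the primary test, make the other main outcomes and the other visit secondary, and reword the power sentence so that 107 participants and alpha 0.05 refer to that test. One workable choice is steps per day, change from baseline to 3-6 months: it needs no intensity cut-point, and the earlier visit is less exposed to construction delay and the end of the grant. It is not the only choice. The Discussion gives total PA particular weight for health benefit, and any variable fixed in advance would cure the defect.

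Alternatively, keep several primary contrasts, state how alpha is divided among them, and restate the power for 107. On the assumptions above, a Bonferroni split would leave about 64 to 65% power with three contrasts and about 55 to 56% with six.

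The first option changes wording only: no data, visits or participants are added, and the primary test keeps its 5% error rate. Its price is that the demoted outcomes can no longer support a primary claim. The second keeps all of them at primary rank, at the price of lower power or a larger sample.

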### Intervention

Based on evidence of BE features that are associated with older adults’ PA, healthy eating, and social connections, as well as preliminary data collected by our team, design recommendations for improving health-promoting features of buildings, sites, and local neighbourhoods are being made. We are working closely with building developers and architecture teams to integrate intervention elements at the building and site scales. We also plan to work with municipalities to integrate intervention elements at the neighbourhood scale where possible. When developers have specifically chosen upcoming sites situated within neighbourhoods with amenities close by, the intervention(s) will also include the existing healthy-features of the neighbourhood(s) (e.g., mixed-use).

Design intervention elements will be tailored to the intervention site(s). The main evidence-based health-promoting features recommended include: more visible stairwells through strategies like open stairwells or stairwells with glazed doors and walls [26]; improvements to stairwell aesthetic and safety designs [27]; indoor and outdoor PA spaces such as multigenerational play and exercise spaces [28]; prompting signage for spaces such as stairs and other amenities [29]; patio/balcony included for each unit with visibility of the patios of other units (based on preliminary research by our team); continuous sidewalks or multi-use paths that connect the building to neighbourhood amenities with benches for resting, pedestrian-scale lighting, and sidewalk handrails or heating [30]; gardening spaces such as greenhouse and/or raised garden beds [31]; bicycle infrastructure such as shared bicycles/adult tricycles, bicycle lanes, and bicycle parking [32]; additional healthy commercial amenities onsite or in neighbourhood [33]; and farmers markets onsite or in neighbourhood [34].

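### The stair-climbing answers overlap at 6 floors, so a resident at exactly 6 can be placed in either of the top two numeric categories

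*Protocol article*

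**What the plan says.** In the protocol article, under Quantitative resident evaluation, Measures (Physical activity), residents are asked: "How many total floors of stairs throughout the day do you walk UP on an average weekday at your CURRENT home building". The answers offered are "0 floors, 1–2 floors, 3–6 floors, 6 or more floors, unable to walk up the stairs".

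The same subsection places this item outside the main outcomes: "The main outcomes of interest are average steps per day, minutes of total PA per day, and minutes of moderate-to-vigorous PA (MVPA) per day". The paragraph on capability, opportunity and motivation gives stair climbing as an example of a behaviour that those questions may cover: "if healthy stairwell design elements are implemented, then stair climbing will likely be included as an outcome". Stairwell design is among the features recommended under Intervention, which include "more visible stairwells through strategies like open stairwells or stairwells with glazed doors and walls".

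The Analyses subsection compares change from baseline between groups at up to two follow-ups. On the choice of model it says "The type of analysis will depend on the measurement unit of each outcome", and gives as examples "linear regression for continuous outcome variables, logistic regression for categorical outcome variables".

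**The concern.** Answer options for a count should cover every value once. Here the value 6 is covered twice, and nothing elsewhere in the article corrects it. The item is asked repeatedly and analysed as change, so an ambiguous boundary can do two things:

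- It can create change: a resident at 6 floors in both waves ticks the lower option once and the upper option once.
- It can hide change: a resident who moves from 5 to 6 floors may stay in the lower option.

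With random ticking the result is noise in the between-group comparison of change. It becomes bias only if the groups differ in how residents move into or out of 6 floors, or in how they resolve the ambiguity. Because stairwell design is among the recommended features, this item is close to one of the mechanisms that the study wants to observe. Once the answers are collected, no analysis rule can recover which side of the boundary a 6-floor resident belonged on.

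**Working it through.** The plan states no figure for this item, so there is none to reproduce. The check has three steps.

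**Step 1. Map each whole number of floors to every numeric option that admits it.** Input: the printed answer list.

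| Floors | Options that fit |
|---|---|
| 0 | 0 |
| 1, 2 | 1–2 |
| 3, 4, 5 | 3–6 |
| 6 | 3–6 and 6 or more |
| 7 and above | 6 or more |

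Only the value 6 fits two numeric options. A split at 0 versus 1 or more, or at 0–2 versus 3 or more, classifies every count the same way whichever box the 6-floor residents tick. Only a comparison that uses the boundary between the top two numeric options is affected.

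**Step 2. Share of residents at exactly 6 floors.** The article gives no distribution, so this is an assumption shown as a range. Let m be the mean number of floors, taken from 1 to 6.

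- Poisson: P(6) = e^(−m) m^6 / 720.
- Geometric starting at 0: P(6) = p(1 − p)^6, with p = 1/(1 + m).

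| Mean m | Poisson P(6) | Geometric P(6) |
|---|---|---|
| 1 | 0.1% | 0.8% |
| 2 | 1.2% | 2.9% |
| 3 | 5.0% | 4.4% |
| 4 | 10.4% | 5.2% |
| 5 | 14.6% | 5.6% |
| 6 | 16.1% | 5.7% |

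Both formulas peak at m = 6, so 16.1% and 5.7% are the ceilings for these two families whatever the mean. Heaping of answers on 6 could exceed them.

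**Step 3. False change between two waves.** Take a resident at exactly 6 floors in both waves who ticks the upper option with probability q, independently each time. Then P(different ticks) = 2q(1 − q). This is largest at q = 0.5, where it equals 0.5, and it is 0 if the resident always resolves the ambiguity the same way.

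- Poisson, upper end: 16.1% × 0.5 = about 8% of residents. At m = 1 the figure is below 0.1%.
- Geometric: 0.8% × 0.5 = 0.4%, up to 5.7% × 0.5 = about 3%.

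For scale, in a sample of 107 the upper ends are 107 × 0.161 × 0.5 ≈ 9 residents (Poisson) and 107 × 0.057 × 0.5 ≈ 3 residents (geometric), across both groups.

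**The case against.** The strongest reply is that this is one secondary self-report item, perhaps only a misprint in the article. Stairwell features are recommendations that the developer may or may not adopt, and the three main activity outcomes come from the accelerometer. All of that stands, and it limits the point to a minor one. It does not remove the overlap, which is in the printed text and cannot be repaired after collection.

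A reader might infer three stronger things that the article does not support.

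- **That the whole outcome is misclassified.** Every count other than 6 fits exactly one numeric option.
- **That the item does not suit the planned analysis.** The article mentions "logistic regression for categorical outcome variables" only as an example and does not say whether the form is binary, multinomial or ordinal. A multinomial model accepts an unordered level, a binary split away from 6 avoids the overlap, and a proportional-odds model is itself a logistic model. No cut point is stated, and an article may leave that choice to the analysis plan.
- **That the answer for residents who cannot climb stairs is a flaw in itself.** It is a capability state among counts, and such a resident also climbs 0 floors, so it has no natural place in an ordering. But it lets the analyst separate those who cannot climb from those who do not. It can be analysed separately, merged or excluded without changing the survey. Stair-climbing limitation is also measured independently by an SF-12 question.

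**Conclusion.** The point holds in a narrow form. As printed, the top two numeric options overlap at exactly 6 floors, and this can produce apparent change between waves without any change in behaviour. That much follows from the text alone.

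The size is small and uncertain. Under the assumed distributions, the share showing a false one-category change between two waves ranges from below 0.1% to about 8% (Poisson), or from 0.4% to about 3% (geometric). The upper figures require a mean near 6 floors and random, independent ticking at each wave, so they are worst cases within those families. Bias between groups is possible, but nothing in the article allows it to be quantified. The accelerometer outcomes, the sample size of 107 and any split of this item away from the 6-floor boundary are unaffected.

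**What to change.** Before baseline, do one of the following:

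- make the numeric options mutually exclusive, for example 0, 1–2, 3–5, and 6 or more floors;
- record the number of floors and group it at analysis; or
- if the survey in use already has no overlap, confirm this and correct the printed list.

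If an ordered model is then used for this item, keep residents who cannot walk up stairs out of the ordered levels and report them separately.

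The cost is a one-line edit to the survey and a small loss of comparability with any earlier data gathered on the old options. The Setting and residents section says that site locations were not yet final, so there appears to be time for the edit.
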